## Abstract

**Background and objectives:**

Periprosthetic aortic regurgitation (PPR) after transcatheter aortic valve implantation (TAVI) remains an important issue associated with impaired long-term outcomes. The current randomised study aims to evaluate potential differences between the balloon-expandable Edwards SAPIEN-3 and the self-expanding Medtronic CoreValve system with the main focus on post-TAVI PPR by means of novel imaging endpoints, and an additional focus on other clinical endpoints.

**Endpoints:**

The primary endpoint of this study is quantitative assessment of the severity of post-procedural PPR using cardiac magnetic resonance imaging. Several other novel imaging modalities (X-ray contrast angiography, echocardiography) are used as secondary imaging modalities for the assessment of PPR following TAVI. Secondary objectives of the study include clinical outcomes such as cerebral and kidney injury related to TAVI, and quality of life.

**Methods and design:**

The ELECT study is a single-centre, prospective, two-armed randomised controlled trial. For the purpose of this study, 108 consecutive adult patients suitable for transfemoral TAVI will be randomly allocated to receive the SAPIEN-3 (*n* = 54) or the CoreValve system (*n* = 54).

**Discussion:**

The ELECT trial is the first randomised controlled trial to quantitatively compare the extent of post-TAVI PPR between the SAPIEN-3 and CoreValve. Furthermore, it will evaluate potential differences between the two prostheses with regard to mid-term clinical outcome and quality of life.

## Background

Transcatheter aortic valve implantation (TAVI) is a valid treatment strategy for patients with severe symptomatic aortic stenosis who are regarded as being at high risk [1, 2] or as unable to undergo open-heart surgery [3]. Two transcatheter heart valves (THVs) based on different technical concepts have been developed and are widely used. These are the balloon-expandable SAPIEN THV (Edwards Lifesciences, Irvine, CA, USA), and the self-expanding CoreValve THV (CV-THV) (Medtronic, Minneapolis, MN, USA). Both THVs have shown excellent clinical results, but each has specific features, advantages and disadvantages [2, 4, 5].

Currently available evidence suggests that TAVI is feasible and provides long-term haemodynamic and clinical improvements, but questions remain concerning the safety and durability of this technique. Several important complications of TAVI have to be addressed in order to warrant the wider use of this procedure [6, 7]. Significant concerns have been raised about the high incidence of post-procedural periprosthetic aortic regurgitation (PPR) [1, 2] which is associated with increased mortality [8–11]. Other important procedural-related complications are cerebrovascular events [12], cardiac conduction disorders [13] and acute kidney injury [14, 15].

It has been estimated that between 41–100% of patients have some degree of PPR following TAVI (mild >45%; moderately severe 2–12%) [10, 16]. Even mild PPR is associated with 10–15% higher mortality after two years in comparison with patients with either no or only a trace of PPR, as shown in the PARTNER cohort A [4]. The extent and severity of native valve and left ventricular outflow tract (LVOT) calcification, undersizing of the valve prosthesis relative to the dimensions of the aortic annulus, suboptimal placement of the prosthesis and incomplete apposition of the stent frame owing to calcification in the device landing zone are all known mechanisms of PPR following TAVI [17]. However, the impact of prosthesis type (S3-THV or CV-THV) on the risk of post-TAVI PPR is less clear.

A few recent reports [17, 18], one of which was the only randomised trial to compare SAPIEN XT-THV (SXT-THV) (Edwards Lifesciences, Irvine, CA, USA) with CV-THV (CHOICE study), have suggested differences in the haemodynamic performance of both THVs where the use of CV-THV was associated with a higher rate of residual PPR. However, the operator’s familiarity with the device and subjective measurement of PPR using unidimensional X‑ray angiography images or two-dimensional (2D) echocardiography may bias the results. Hence, an adequately powered randomised study using quantitative assessment techniques may clarify the difference in severity of PPR between SXT-THV and CV-THV more reliably.

Although 2D echocardiography is currently considered the reference standard for evaluation and grading of aortic regurgitation, PPR is difficult to detect and quantify using conventional 2D echocardiography. In PPR, eccentric jets may become entrained along the left ventricular wall, which tends to alter their appearance and hence the perception of PPR severity [19]. Moreover, the possible presence of multiple jets originating from different periprosthetic locations makes their cumulative impact on the overall importance of PPR difficult to judge. Furthermore, in obese patients and patients with chronic obstructive pulmonary disease, the acoustic window at transthoracic echocardiography may be inadequate for comprehensive examination of the valves. Finally, this evaluation is also subject to inter- and intra-observer variability. For these reasons, other diagnostic modalities such as three-dimensional transoesophageal echocardiography (3D-TEE) [20, 21], phase contrast magnetic resonance imaging (MRI) [22], and X‑ray contrast aortography [23] have been proposed for quantification of PPR after TAVI. These modalities can be used to measure the severity of aortic regurgitation by quantifying regurgitant volume and regurgitant fraction, thus minimising observer dependency.

Recently, the SAPIEN-3 THV (S3-THV) (Edwards Lifesciences, Irvine, CA, USA) was introduced [24] which, besides a differently designed stent frame, has an additional outer skirt in order to minimise post-TAVI PPR [5, 25]. However, whether this new feature will be effective in preventing post-TAVI PPR in daily practice remains to be established as well as the direct comparison versus the CV-THV. We designed a clinical trial for the randomised comparison of S3-THV and CV-THV in a routine TAVI population focusing primarily on post-TAVI PPR measured by different innovative imaging modalities, which allow a more accurate and observer-independent quantification of the PPR.

## Methods and design

The ELECT study is a single-centre, prospective, two-armed randomised controlled trial. Consecutive adult males or females, judged eligible for transfemoral TAVI by the local multidisciplinary heart team, and meeting the inclusion criteria will be approached for inclusion in this study. Device size selection will be based on charts provided by the manufacturer and on the pre-procedural multislice computed tomography (MSCT) annular perimeter. The ELECT trial has been designed in accordance with the ethical principles of the Declaration of Helsinki. The Ethics Committee of the University Medical Center Utrecht has given its full approval for the study and patients who agree to participate will be asked for written informed consent.

### Inclusion criteria

In order to be eligible to participate in this study, subjects must meet all of the following criteria: The patient must be ≥18 years of age and diagnosed with severe symptomatic aortic stenosis, judged inoperable or at high surgical risk (EuroSCORE >15% or other criteria that make surgery high risk by a consensus among cardiologists and cardiac surgeons in the heart team) and deemed eligible for transfemoral TAVI. The diameter of the aortic annulus diameter should be ≥18 and ≤28 mm assessed with MSCT. There should be no contraindications to study requirements such as MRI or TEE.

### Exclusion criteria

Patients unable or unwilling to give informed consent are excluded from this study, as are patients whose aortic annulus diameter does not meet the inclusion criteria.

### Randomisation and interventions

Patients who meet all the inclusion criteria and none of the exclusion criteria will be randomised in consecutive order. After successful puncture of the femoral artery chosen as entry site for TAVI, subjects will be randomised in a 1:1 fashion using sealed envelopes, to receive either an S3-THV or a CV-THV (Fig. 1).

**Fig. 1 Fig1:**
[figure not shown]
Flowchart of the study

Both prostheses (S3-THV and CV-THV) have received the CE mark of approval for the treatment of severe aortic stenosis. Determination of prosthesis size is based on the aortic annulus diameter, using pre-procedural contrast-enhanced MSCT. The S3-THV is provided in three sizes: 23 mm, 26 mm and 29 mm (for native annulus diameters 18–22 mm, 21–25 mm, and 24–28 mm, respectively). The self-expanding CV-THV is available in four sizes: 23 mm, 26 mm, 29 mm and 31 mm (for native aortic annulus diameters 18–20 mm, 20–23 mm, 23–27 mm, and 27–28 mm, respectively). In order to be able to randomise patients to receive S3-THV or CV-THV, only patients with an annular diameter range between ≥18 and ≤28 mm will be included in this study.

### TAVI procedure

All procedures will be performed by a highly experienced team with extensive knowledge of both devices. Details of the implantation technique for both S3-THVand CV-THV have been previously reported [10, 24, 26, 27]. The procedure is routinely performed under conscious sedation with local anaesthesia. Fluoroscopy and intracardiac echocardiography are used for procedural guidance [28]. Balloon pre-dilatation is performed in all cases in accordance with our routine. Valve deployment is routinely done under rapid pacing (S3-THV 180 beats/min) or stabilising pacing (CV-THV 120 beats/min). Patients are monitored for at least 72 h and discharged on a regimen of lifelong low-dose aspirin (80–100 mg per day), or an oral anticoagulant (if there is a clinical indication for this), and 3 months of clopidogrel (75 mg per day).

### Endpoint assessment

Follow-up assessments for the measurements of the primary and secondary endpoints will be performed at specified time points.

### Primary endpoint

The primary endpoint of this study is quantitative assessment of the severity of post-procedural PPR using CMR. At day 4 (+1) after TAVI, patients without contraindications for MRI will undergo cardiac phase contrast MRI for quantitative grading of PPR according to the standard grading criteria.

### Secondary endpoints

The secondary endpoints of this study include assessment of PPR using other novel imaging modalities including X‑ray contrast angiography, and echocardiography (TTE and TEE). Furthermore, all clinical endpoints as defined by VARC-2 [29] and the quality of life questionnaires will be collected.

Contrast X‑ray angiography is performed at the end of each TAVI procedure in order to measure the degree of post-implantation PPR by contrast densitometry (CAAS A‑valve quantitative regurgitation analysis; Pie Medical Imaging, Maastricht, the Netherlands) (Fig. 2). Technical details of this approach have been reported previously [23].

**Fig. 2 Fig2:**
[figure not shown]
X-ray contrast densitometry with the special software (CAAS A‑Valve) after transcatheter aortic valve implantation

Echocardiography, including TTE and TEE, is performed within five days following TAVI. The use of the Doppler technique provides accurate information on the number and severity of paravalvular jets. In addition, 3D TEE is used to analyse the complete morphology of the PPR colour flow stream in the region of its origin. Consequently, views from any level can be obtained, and the direction and extension of PPR jets can be assessed. New dedicated analysis software (Personal Space Technologies BV, the Netherlands) designed for the visualisation and analysis of 3D volumetric echocardiography data will be used for the quantitative grading of PPR severity in this study.

Patients will undergo cerebral MRI including a diffusion-weighted imaging sequence on day 4 (+1) after TAVI, for detection of new cerebral ischaemic injury [30]. In order to detect kidney injury related to TAVI, serum and urine samples (including 24-hour urine) will be collected. Acute kidney injury will be assessed within 5 days after TAVI and compared with baseline. Irreversible kidney injury (VARC-2) will be assessed at 6‑month follow-up. In order to investigate possible mid-term changes in post-TAVI PPR, valvular function will be evaluated at 6 months using TTE and 3D TEE as described above. Finally, validated quality of life questionnaires (KCC-Q, EuroQol EQ-5D and SF-36) will be used to measure health-related quality of life at one year follow-up and compared with baseline (Fig. 3).

**Fig. 3 Fig3:**
[figure not shown]
Planned flow diagram during ELECT trial

## Statistical analysis

Descriptive statistics will be used to ascertain any imbalance between the arms at baseline. The extent of missing data will be reported and baseline factors will be compared for completers and non-completers to assess the extent of any bias that may result.

Continuous variables are presented as means ± standard deviation or medians [interquartile range], as considered appropriate, and categorical variables as counts and percentages. Continuous variables will be compared using the Student *t* test or Mann-Whitney test, depending on data distribution. Categorical variables will be compared using chi-square or Fisher’s exact test, as considered appropriate. For the analysis of the difference in PPR between each of the prostheses, log transformation will be performed on the regurgitation volume data before performing a *t* test, as these data are expected to be right-skewed. The follow-up analysis for changes in the endpoints in the time within the arms will be performed using the paired *t* test and the repeated measurements analysis of variance. A two-tailed *p*-value of less than 0.05 is regarded as statistically significant. All analyses will be performed according to the intention-to-treat principle. Data will be analysed using IBM SPSS Statistics software version 20 (IBM Corp., Armonk, NY, USA), and R version 2.12.0 (http://www.r-project.org).

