### Sample size calculation

A sample size calculation for the primary endpoint post-TAVI PPR has been performed. A literature search on the difference in the extent of PPR after TAVI between the S3-THV and CV-THV prostheses has been done. No studies were found that included a quantitative PPR comparison between these two prostheses. We used data from 25 patients treated with TAVI at our centre for a sample size calculation. PPR quantification in these patients was performed using cardiac MRI. Because the distribution of these volume data was skewed to the right, we performed a log transformation on the original data to improve approximations to normality (original volumes presented as ml). The log transformed values were as follows: an overall mean regurgitant volume of 0.48, an ‘overall’ median regurgitant volume of 0.48, an overall standard deviation (SD) of 0.53, and a mean regurgitant volume of 0.32 for S3-THV and a mean regurgitant volume of 0.63 for CV-THV. CMR grades of PPR will be defined according to regurgitation fraction using similar reference cut-point values according to the standard grading criteria. As even mild PPR has been shown to be associated with long-term mortality, any significant difference in post-TAVI PPR volume between S3-THV and CV-THV is considered clinically important. The sample size calculation, including the above-mentioned log transformed values for mean regurgitant volumes and standard deviations, yielded a sample size of 49 patients in each arm to show superiority or equivalence over S3-THV and CV-THV with a power of 80%. As we took an expected dropout rate of 10% into account, this yielded a total sample size of 54 patients in each arm.

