Interestingly, the recently published results of the CoreValve US Pivotal Trial [32] showed that the incidence of any PPR after the implantation of CV-THV decreases over time: 41.1% at discharge and 31.9% at one year. The latter was also accompanied by a reduction in the incidence of more-than-mild aortic regurgitation during follow-up, at 13.8% at discharge, 10.1% at 6 months, and 6.4% at one year. This suggests that measurement of post-TAVI PPR in the CV-THV during the few first days after TAVI will probably overestimate its long-term severity. In the ELECT study, the severity of PPR is also measured at 6‑month follow-up using transthoracic and 3D transoesophageal echocardiography, which allows for a more reliable comparison between the two prostheses.

One previously published meta-analysis [25] showed a higher risk of moderate or severe post-procedural PPR after CV-THV implantation (16%) as compared with E﻿d﻿w﻿a﻿r﻿d﻿s SAPIEN implantation (9.1%, *p* = 0.005). The CHOICE study [18], which is the only randomised head-to-head trial to date that has compared the balloon-expandable SXT-THV with the CV-THV system, reported a significant difference in the frequency of any degree of PPR (38% in SXT group versus 65% in the CV group, *p* < 0.001) and more-than-mild PPR (4.1% in SXT group versus 18.3% in the CV group, *p* < 0.001 by angiography) favouring the balloon-expandable valve. However, the extent of the PPR in the CHOICE trial was measured using aortic root angiography immediately after prosthesis implantation, which is an important limitation of this clinical trial.

On the other hand, the PRAGMATIC [33] study reported a very low and comparable incidence of more-than-mild PPR with both Edwards SAPIEN and CV-THV (1.8% and 2.0%, respectively) in a large multicentre propensity score-matched study. Recently, another study among a selected group of patients receiving S3-THV or CV-THV reported a significantly lower rate of mild or severe PPR, lower need for permanent pacemaker implantation, and higher rate of device success for the S3-THV compared with CV-THV. However, this study was limited by its design and small sample size [34].

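### Secondary analyses of PPR in three or more ordered grades: the categorical rule ignores the order, and an order-using test is a cheap, minor improvement

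*Protocol article*

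**What the plan says.** In the protocol article, Statistical analysis, the rule for categorical data is "Categorical variables will be compared using chi-square or" Fisher's exact test, and the discretion that follows is a choice between those two. The only rank test belongs to another rule: "Continuous variables will be compared using the Student" t test or the Mann-Whitney test. The one analysis written specifically for PPR concerns volume: "log transformation will be performed on the regurgitation volume data before performing a" t test.

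Grades enter in three places. The Primary endpoint section describes "cardiac phase contrast MRI for quantitative grading of PPR according to the standard grading criteria". The Sample size calculation section adds that "CMR grades of PPR will be defined according to regurgitation fraction", with reference cut-points. The Secondary endpoints section says of the dedicated 3D echocardiography software that it "will be used for the quantitative grading of PPR severity in this study", and it repeats the TTE and 3D TEE assessment at 6 months. No trend, rank or proportional-odds method is named for ordered categories.

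**The concern.** Grades cut from regurgitation fraction are ordered by construction, and the question asked of them has a direction: which valve leaks more. Chi-square and Fisher's exact test on a table with three or more columns use neither fact. They spread the test over every way in which the two distributions can differ, so they are less sensitive to a consistent shift towards worse grades, and a significant result does not in itself say that one valve is worse. At stake is some power, and a single effect estimate, in the secondary comparisons of PPR grade.

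**Working it through.** **1. The plan's own sample size, to show what is not in dispute.** Inputs from Sample size calculation: means of log volume 0.32 and 0.63 (difference 0.31), SD 0.53, power 80%; two-sided 0.05 from Statistical analysis. n per arm = 2(1.960 + 0.842)² × 0.53² / 0.31² = 15.70 × 0.2809 / 0.0961 = 45.9, so 46; the exact t-test calculation gives 47. With the difference rounded to 0.30 the formula gives 49, the stated figure. Dropout: 49 × 1.1 = 53.9, so 54 as stated (49 / 0.9 gives 55). The calculation is for log volume and does not involve grades.

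**2. What the test ignores.** Take an invented table at 49 per arm, with none / mild / more than mild = 30/16/3 v 17/23/9. Expected counts are 23.5, 19.5 and 6 in each arm.
- Chi-square = 2 × (6.5²/23.5 + 3.5²/19.5 + 3²/6) = 2 × (1.798 + 0.628 + 1.500) = 7.85 on 2 df, p = 0.020. The value is the same if the grade columns are permuted or the arms exchanged.
- A rank comparison looks at the 49 × 49 = 2401 between-arm pairs. The second arm is worse in 30 × 32 + 16 × 9 = 1104, tied in 30 × 17 + 16 × 23 + 3 × 9 = 905, and better in 392. Its chance of the worse grade, counting ties as half, is (1104 + 452.5)/2401 = 0.65. With tie correction z = (1556.5 − 1200.5)/127.8 = 2.79, p = 0.005. This statistic has a sign.

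**3. Power with three grades.** The Discussion quotes any PPR as "38% in SXT group versus 65% in the CV group", and more-than-mild PPR as 4.1% v 18.3%. By subtraction: none 62% v 35%, mild 33.9% v 46.7%, more than mild 4.1% v 18.3%. Simulated trials, two-sided 0.05:

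| Per arm | Chi-square | Fisher | Wilcoxon, tie-corrected |
|---|---|---|---|
| 49 | 80% | 78% | 86% |
| 54 | 84% | 84% | 89% |

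Chi-square needs about 56 per arm to match Wilcoxon at 49.

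**4. Four grades, by assumption.** The documents do not divide more-than-mild PPR. If it is split 75/25 into moderate and severe, power at 49 per arm is about 73% for chi-square and 86% for Wilcoxon, and chi-square needs about 65 per arm to match. Fisher's test suits these sparse cells better and recovers part of the gap: 77%, against 74% for chi-square in the same 4,000 simulated trials.

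**5. Smaller effects, also assumed.** Proportional-odds shift at 49 per arm, chi-square v Wilcoxon. Three grades starting from 62/33.9/4.1%: 32% v 41% at an odds ratio of 2, and 69% v 79% at 3. Four grades starting from 45/35/15/5%: 30% v 45%, and 68% v 84%.

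**6. A case that goes the other way.** With 50/30/20% v 40/55/5%, where the grades do not shift in one direction, chi-square has 77% power and Wilcoxon about 5%.

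**The case against.** The strongest reply is that the directional question already has its own analysis. The t test on log regurgitant volume is signed, uses the continuous measurement and is the comparison on which the trial was sized. This stands in full.

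Next, the article nowhere says that grades will be compared between the valves by chi-square. That follows only because a grade is categorical and no other rule covers it. The echocardiography and densitometry results may be analysed as volumes or fractions, which fall under the continuous rule, or as two-class contrasts such as any PPR or more-than-mild PPR, where there is no order to lose. This also stands, and it confines the point to readings reported in three or more ordered grades.

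Third, the stated tests are valid: simulated type I error is about 5% or less. The planned counts and percentages would also let a reader see which valve has the worse grades. So it is the test that lacks direction, not the report.

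Finally, a condensed article may leave the test for each secondary reading to a fuller document. That carries less weight here, because the article does state a general rule, and read as written it assigns ordered grades to an unordered test.

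A reader might infer that the trial has chosen the wrong test for its main question, is underpowered, or cannot show which valve leaks more. The documents support none of these.

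**Conclusion.** The point holds as a minor, low-cost improvement to secondary analyses. Where PPR is reported in three or more ordered grades, the only rule that covers it ignores the order. On the rates given in the protocol the loss is about 6 percentage points of power at 49 per arm (80% v 86%) and about 5 at 54 (84% v 89%). Larger gaps, such as 73% v 86% with four grades, depend on an assumed split and narrow somewhat if Fisher's test is used.

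The figures rest on three assumptions: that grades are compared between the valves under the general categorical rule; that the shift is in one direction, as in the quoted trial, where both any PPR and more-than-mild PPR were higher with the self-expanding valve; and that rates from an earlier balloon-expandable valve, read by angiography, are a fair illustration. They are not a forecast for this trial. The primary comparison, the sample size, and binary or continuous PPR readings are untouched.

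**What to change.** In Statistical analysis, limit chi-square and Fisher's exact test to binary and unordered variables. Add that PPR reported in three or more ordered grades (CMR, and any graded TTE or TEE reading, early and at 6 months) will be compared by a tie-corrected Wilcoxon-Mann-Whitney test or a proportional-odds model, with a common odds ratio and 95% confidence interval beside the counts and percentages.

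This costs a sentence or two, and no data or patients. There are two downsides to accept. Power is lower if the grades do not shift in one direction. The single odds ratio also relies on proportional odds, which the rank test itself does not need. In the quoted rates the two cumulative odds ratios are (0.62/0.38)/(0.35/0.65) = 3.0 and (0.959/0.041)/(0.817/0.183) = 5.2, so the assumption is worth examining and the full grade table should always be shown.

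### The primary t test leaves pre-randomisation MSCT information unused; a pre-specified adjusted model would cost almost nothing, for a gain in precision of unknown size (minor)

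*Protocol article*

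**What the plan says.** **Primary comparison** (Statistical analysis): "For the analysis of the difference in PPR between each of the prostheses, log transformation will be performed on the regurgitation volume data". The logged volumes then go into a two-group t test; expected right skew is the reason given for taking logs. No covariate is named. The significance rule is "A two-tailed *p*-value of less than 0.05 is regarded as statistically significant".

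**Baseline differences** (Statistical analysis): "Descriptive statistics will be used to ascertain any imbalance between the arms at baseline". Nothing is said about what follows if an imbalance is found.

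**Allocation** (Randomisation and interventions): 1:1 by sealed envelope, after successful femoral puncture. No stratification factor is stated.

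**What is known before allocation:** annulus diameter on MSCT decides eligibility, with 18 to 28 mm required (Inclusion criteria). It also decides device size: "Determination of prosthesis size is based on the aortic annulus diameter, using pre-procedural contrast-enhanced MSCT" (Randomisation and interventions, text after Fig. 1). Methods and design likewise ties size selection to the pre-procedural MSCT.

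**Mechanisms of PPR** (Background): the article lists native valve and outflow-tract calcification, a prosthesis too small for the annulus, poor placement, and poor apposition caused by calcification. It says these "are all known mechanisms of PPR following TAVI".

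**Planning values** (Sample size calculation): on the log scale, "a mean regurgitant volume of 0.32 for S3-THV and a mean regurgitant volume of 0.63 for CV-THV", with an overall SD of 0.53. The stated result is 49 per arm for 80% power, raised to 54 for 10% dropout.

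**The concern.** The article fixes a specific test for its primary endpoint, so this is a stated choice and not merely detail left to another document. That test uses no baseline information, although a continuous MSCT measurement exists for everyone and the article itself names a baseline anatomical feature, calcification, as a mechanism of the outcome.

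Two things are at stake, both modest:

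- **Precision.** If baseline anatomy explains part of the variation in regurgitant volume, an adjusted model gives a narrower interval and more power from the same patients.
- **Credibility of the single result.** Baseline imbalance is to be described, but no adjusted analysis is pre-specified. If an imbalance appears, any adjustment added then would be post hoc.

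**Working it through.** **Inputs.** Difference d = 0.63 − 0.32 = 0.31 and SD = 0.53, both on the log scale, with 49 per arm (Sample size calculation). Two-sided alpha is 0.05 (Statistical analysis). The overall SD is used as the within-arm SD.

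**1. The plan's own figure.** The normal approximation gives n = 2 × [0.53 × (1.960 + 0.842) / 0.31]² = 45.9, so 46 per arm. The noncentral t calculation gives 47 per arm (80.1% power). Rounding the difference to 0.30 gives 49 exactly. The stated 49 is therefore reproduced to within two patients. For dropout, 49 × 1.10 = 53.9, hence 54; conversely 54 × 0.90 = 48.6, so about 49 evaluable per arm is the right basis for what follows.

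**2. Power of the planned test at 49 per arm.** SE = 0.53 × √(2/49) = 0.107. Noncentrality = 0.31 / 0.107 = 2.90 on 96 degrees of freedom. Power = 81.8%.

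**3. Power with one baseline covariate.** Let R² be the share of variance in log regurgitant volume that the covariate explains. Residual SD = 0.53 × √(1 − R²), with 95 degrees of freedom. The article gives no R², so a range is shown.

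| Assumed R² | Residual SD | Power at 49 per arm | Gain over the t test (points) |
|---|---|---|---|
| 0 | 0.530 | 81.7% | −0.01 |
| 0.01 | 0.527 | 82.1% | 0.4 |
| 0.04 | 0.519 | 83.3% | 1.5 |
| 0.10 | 0.503 | 85.6% | 3.8 |
| 0.20 | 0.474 | 89.3% | 7.6 |

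Unrounded, power at R² = 0 is 81.75% against 81.76% for the t test. With two covariates (94 degrees of freedom) it is 81.74%. The interval narrows by the factor √(1 − R²): about 5% at R² = 0.10 and 11% at R² = 0.20.

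**4. A limit of the table.** It counts only the degree of freedom and treats the covariate as balanced between arms. Chance imbalance in one covariate inflates the variance of the adjusted estimate by about 1/(2 × 49 − 4) = 1/94 on average, or about 1%. That is worth half a patient per arm. Power changes by 0.8 point between 48 and 49 per arm (81.0% to 81.8%), so this costs about 0.4 point. It offsets the gain at R² = 0.01 and matters little at R² = 0.04 and above.

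**5. Chance imbalance under the unadjusted test.** The standardised difference in a covariate between arms has SD √(2/49) = 0.202. A difference of at least 0.3 SD therefore has probability 2 × [1 − Φ(0.3/0.202)] = 14%. A 0.3 SD imbalance moves the unadjusted estimate by 0.3 × √R² × 0.53:

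- R² = 0.04: 0.032, or 10% of the planned 0.31
- R² = 0.10: 0.050, or 16%
- R² = 0.20: 0.071, or 23%

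Each of these is smaller than one standard error (0.107), and the t test's standard error already allows for this variation.

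**The case against.** **The planned test is not wrong.** This stands in full. A t test after 1:1 randomisation is unbiased, its type I error allows for chance imbalance, and the sample size was planned for it and delivers its 80%. A reader might infer that the primary estimate is biased or that the trial is underpowered without adjustment; nothing in the article supports either.

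**Annulus size is not a named mechanism of PPR.** This also stands. A reader might infer from the Background that it is. The text names a prosthesis too small for the annulus, which depends on the allocated device and its own size bands and is therefore settled after randomisation. The article does not rank the mechanisms either, so neither annulus size nor calcification can be called the strongest predictor. Each device is sized to the annulus and the range is restricted to 18 to 28 mm, so raw annulus diameter may be only weakly related to regurgitant volume.

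**The better-supported covariate may not be free.** This stands. Calcification is named in the Background, but the article describes MSCT only for annulus measurement and device sizing and does not say that calcification is graded.

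**Adjustment may appear in a fuller document.** Possible, and it limits the weight of the point: neither the full protocol nor an analysis plan is at hand, and an article's silence on stratification does not show there is none. It does not remove the point, because the article does state the primary test, and that test is unadjusted.

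**Conclusion.** The point holds as a minor efficiency improvement. The stated primary analysis is valid and meets its planned power (81.8% at 49 per arm), but it leaves unused a pre-randomisation measurement that every patient has, and a baseline mechanism the article names.

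The gain cannot be determined from the article. It is negligible if the covariates explain about 1% of the variance, about 1.5 points of power at 4%, about 4 points at 10% and 7 to 8 points at 20%. The possible loss is very small: under 0.1 point from the degree of freedom, or about 0.4 point once chance imbalance in one uninformative covariate is counted.

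These figures rest on the article's planning values, on 49 evaluable patients per arm and on assumed values of R². Wording such as lost power, bias or ignored leading predictors would go beyond what the article supports.

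**What to change.** Pre-specify the primary analysis as a linear model of log regurgitant volume on treatment arm and MSCT annulus size, entered as a continuous term. Add calcification if it is already recorded from the pre-procedural scan. Report the adjusted difference with its 95% confidence interval, and keep the unadjusted t test as a supporting analysis.

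Fix the covariates before outcome data are seen, whatever the baseline table shows. Exclude variables determined after randomisation, such as implanted size, degree of oversizing, implantation depth and post-dilatation: they may lie on the path from device to regurgitation, and adjusting for them would change the question.

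**Cost.** A change of wording in the analysis section; annulus size needs no new data. If calcification is not recorded, grading it would mean re-reading existing scans, and the model can go ahead without it. The sample size need not change.
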